### *Sample size requirements*

### Sample size requirements for a cluster-randomised trial15 were calculated for the primary endpoint of the proportion of patients receiving appropriate treatment (in line with parasitological status). Appropriate treatment is defined as a composite including both a) those who are slide-positive who purchase an ACT and b) those who are slide-negative who do not purchase an ACT or other antimalarial drug. As the priority for improving treatment in the private sector is to increase the proportion of true cases that purchase and use an ACT (as opposed to antipyretics only, without any antimalarial treatment), we do not include prompt appropriate treatment within 24 hours as the primary endpoint in this work package.

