### The study will be undertaken in two sub-counties, and census enumeration areas will be randomized to either intervention or control. Registered drug shops located in intervention areas will receive training in the use of rapid diagnostic test for malaria (RDTs) and supplied with RDTs by the research team, and trained to only recommend antimalarial treatment with Coartem® after a positive test result. In the control areas, registered drug shops will continue to dispense antimalarial treatment based on presumptive diagnosis (current practice).

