### RDTs have recently been introduced into government health facilities in Uganda. Government health staff in the study area will therefore receive additional supportive training to use RDTs and to only provide treatment with Coartem® after a positive result. The study will ensure that public health facilities are well stocked with RDTs, antimalarials and other essential drugs through the government credit supply system. Community sensitization meetings will be carried out to increase awareness of ACTs, reasons for the new treatment policy for malaria, the need for better diagnosis, and importance of adherence to treatment.

| **Private facilities (pharmacies and drug shops)** |
| --- |
| Drug shops randomised to either:  1) Confirmatory diagnosis with RDTs, followed by sale of a commercially-available ACTs only to those who have a positive RDTs  **or**  2) Current practice:  Presumptive clinical diagnosis and treatment of fever |

*Key strengths to the study site*

- - Multiple sampling points within the same district and health system
  - Study design allows comparison between private and public health care providers to assess patient preferences

This allows direct comparison of the effectiveness of treatment, and the cost-effectiveness of improved diagnosis, in a range of different health care providers within the same country.

*Primary endpoints*

- Proportion of patients receiving appropriate treatment from a commercial drug outlet: % of patients diagnosed with malaria who receive appropriate[[1]](#footnote-2) ACT treatment (irrespective of time since onset of treatment).
- Over-prescription: % of patients, who are not parasite-positive, who receive inappropriate ACT treatment from a commercial drug outlet.
- Provider adherence to RDT result: % of patients who receive appropriate treatment, consistent with RDT result
- Cost-effectiveness of RDT compared to presumptive treatment in home management of uncomplicated malaria.

All endpoints will be examined and reported according to age and sex: children aged 0-4y, 5-15y and adults ≥ 16y. For each age group, the proportion of patients receiving appropriate treatment will be compared between shops with RDTs and shops without RDTs, in order to determine whether diagnostic testing reduces overuse of antimalarials in that age group.

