***Methods***

*Diagnosis and treatment procedures*

Private providers will be trained on how to recognize and distinguish uncomplicated & severe malaria, supplying unit-dose packaged Coartem® to customers with uncomplicated malaria, and administration of rectal artesunate pre-referral treatment and referral for children with severe and complicated malaria. Rectal artesunate will be provided free of charge for children with severe malaria who cannot take oral medication.Shops will be provided with low literacy visual aids to help explain the symptoms, diagnosis, correct treatment of malaria and danger signs. The shopkeepers will explain the pictorial instructions to customers, as well as give instructions on dosing and how to give the drug to the patient.

Private providers in the intervention areas will be trained in use and interpretation of the rapid diagnostic test. Shops will be supplied with RDTs and a placard identifying them as an approved provider of malaria diagnostic tests. Private providers will be allowed to sell the test, at a price determined by pre-intervention willingness-to-pay studies. The age and sex of patient, onset of symptoms and promptness of treatment-seeking, diagnosis (including RDT result, where appropriate), tablets supplied and outcome of treatment will be recorded by dispensers. Drug sellers will also be trained in the preparation of thick blood films for malaria, and a research blood slide will be prepared from all patients being treated with an antimalarial drug (irrespective of use of RDT) for later validation of diagnosis and treatment by microscopy. All drug sellers will be trained on good laboratory practices, proper disposal of sharps etc. Sharps containers will be provided, and collected regularly for correct disposal at the health facility by the research team.

Consent will be obtained from drug shop owners to participate in the trial, and for randomization of shops to receive RDTs.

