***Evaluation***

*Appropriateness of treatment and/or referral*

Prescription patterns and drug sales in private shops and clinics will be measured through the use of exit interviews, drug sales records and mystery shopper visits. Drug sales records will be adapted to include data on RDT results. Semi-structured exit interviews will be used to ascertain whether diagnostic testing was offered, was accepted by the patient, and type and quantity of drugs sold. Exit interviews will also investigate the patient’s perception of diagnostic testing and their knowledge and understanding of the test result, treatment advice and/or referral. In non-intervention areas, a finger-prick blood sample will be taken to prepare a research blood film to ascertain by microscopy whether the fever was due to malaria. A random sample of patients will also be followed at home after several days to ascertain adherence to treatment (see section below), outcome of the illness and total household expenditure on treatment. Patients will be recruited on exit from the drug outlet and individual informed consent will be sought from patients (parents or guardians, in the case of minors) to participate in an exit interview and any subsequent household visits.

The appropriateness of treatment provided will be evaluated as the proportion of correctly treated malaria cases, based on the “gold standard” of the research blood slide read by an experienced research technician. Appropriate treatment of fever is a composite definition including both a) those who a slide-positive who are given a 1st-line antimalarial and b) those who are slide-negative who are not given a 1st-line antimalarial. Over-prescription will also be assessed as the proportion of children who are not parasite positive who receive inappropriate ACT treatment.

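### The primary composite is defined in two ways: one section scores ACT purchase, the others score an undefined first-line antimalarial, and the two rules differ for slide-negative and possibly for slide-positive patients

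*Protocol*

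**What the plan says.** All references are to the protocol, section (c).

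- **Sample size requirements.** The composite counts as successes "a) those who are slide-positive who purchase an ACT" and "those who are slide-negative who do not purchase an ACT or other antimalarial drug". The planning rates that follow are stated as ACT purchase: 50% at baseline, rising to 75% in RDT-positive patients, with inappropriate treatment of RDT-negative patients falling to 20%.
- **Evaluation, Appropriateness of treatment and/or referral.** The composite counts "a) those who a slide-positive who are given a 1st-line antimalarial" and "those who are slide-negative who are not given a 1st-line antimalarial".
- **Footnote 1.** It is attached to the first primary endpoint and repeats the Evaluation rule, adding that dosing does not matter.
- **Study design.** Intervention shops are "trained to only recommend antimalarial treatment with Coartem® after a positive test result". The table of private facilities describes the same arm as testing "followed by sale of a commercially-available ACTs only to those who have a positive RDTs".
- **Diagnosis and treatment procedures.** Private providers, with no restriction to one arm, are trained in "supplying unit-dose packaged Coartem® to customers with uncomplicated malaria".

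The protocol nowhere says which drugs are first-line.

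**The concern.** A primary endpoint needs one scoring rule. Here the rule used to size the trial differs from the rule attached to the endpoint list and repeated for the evaluation. Two kinds of sale can change score:

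1. **Slide-positive patient sold an ACT other than the first-line product.** Success under Sample size requirements. Failure under Evaluation and footnote 1 if first-line is narrower than ACT. The design table appears to permit such a sale, so a shop could follow the plan and still be scored either way.
2. **Slide-negative patient sold an antimalarial that is not first-line.** Failure under Sample size requirements, success under Evaluation and footnote 1. For non-ACT drugs this holds even if first-line means any ACT. The Aim section expects such drugs on the market: it hypothesises a shift towards ACTs and away from monotherapy and cheaper combinations.

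If this is left open, the definition could be settled after the data are seen, and the stated power belongs to only one of the two versions.

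**Working it through.** **Step 1: which rule the sample size uses.** Inputs from Sample size requirements: p0 = 0.50, p1 = 0.75, k = 0.25, m = 61 per cluster, 90% power, 5% level (two-sided assumed).

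Clusters per arm = (1.960 + 1.282)² × [p0(1−p0)/m + p1(1−p1)/m + k²(p0² + p1²)] / (p1 − p0)²
= 10.507 × [0.00410 + 0.00307 + 0.05078] / 0.0625 = 9.74, rounded up to 10.

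This reproduces the stated 10 clusters per arm, with no extra cluster added. The inputs are ACT-purchase rates, so the planned power belongs to the ACT wording.

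**Step 2: slide-positive group alone under a narrow first-line rule.** Let s be the share of ACT sales that are other ACTs. The protocol does not give s; 20% is an assumption. Each rate becomes (ACT rate) × (1 − s).

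| Where s = 20% applies | Control vs RDT arm | Difference | Clusters needed | Power with 10 |
|---|---|---|---|---|
| nowhere | 50% vs 75% | 25 points | 9.74 | 0.91 |
| both arms | 40% vs 60% | 20 points | 10.6 | 0.88 |
| control only | 40% vs 75% | 35 points | 4.5 | >0.99 |
| RDT arm only | 50% vs 60% | 10 points | 48.5 | 0.31 |

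**Step 3: whole composite.** Evaluation and footnote 1 apply the first-line test to both groups, so another ACT turns a slide-positive into a failure and a slide-negative into a success. Let p be slide positivity (not given; 30% to 70% assumed). Further assumptions: RDT and slide results agree, s is the same in positives and negatives, the 50% baseline applies to all consultations as the section words it, and the 20% of treated negatives in the RDT arm received an ACT.

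- Planned difference = 25p + 30(1 − p) points: 28.5, 27.5 and 26.5 at p = 30%, 50% and 70%.
- Control change = −s × 0.50 × p + s × 0.50 × (1 − p) = s × 0.50 × (1 − 2p).
- RDT-arm change = −s × 0.75 × p + s × 0.20 × (1 − p).

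At s = 20%:

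| p | Control change | RDT-arm change | Effect, s in control only | Effect, s in both | Effect, s in RDT arm only |
|---|---|---|---|---|---|
| 30% | +4.0 | −1.7 | −4.0 | −5.7 | −1.7 |
| 50% | 0 | −5.5 | 0 | −5.5 | −5.5 |
| 70% | −4.0 | −9.3 | +4.0 | −5.3 | −9.3 |

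Entries are percentage points; an effect column is the RDT-arm change minus the control change where each applies. The sign depends on p and on the arm, and the document gives neither p nor s.

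**Step 4: non-ACT antimalarials.** Let u be the proportion of slide-negatives in an arm who are sold a non-ACT, non-first-line antimalarial and no ACT. Moving from the Sample size rule to the Evaluation rule adds u × (1 − p) to that arm's composite. This term needs no narrow reading of first-line, and u is not given either.

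**The case against.** **The terms may be synonyms.** Footnote 1 hangs on an endpoint worded as ACT treatment, and Evaluation passes from first-line antimalarial to ACT within consecutive sentences. On that reading no slide-positive patient changes score. This is a fair reading and may be what was meant, but the text does not establish it, and other passages single out one ACT product. It also leaves the slide-negative conflict untouched.

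**A statistical analysis plan may list the first-line drugs.** It may. But the protocol itself fixes the composite in two versions, and a later list cannot agree with both on slide-negatives.

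**Study design and its table need not conflict.** One describes what shops recommend, the other what they sell, and the recommended product may itself be commercially available. That weakens the contradiction. It still leaves open whether sale of another ACT is within the intervention.

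**A stronger reading: bias in favour of the RDT arm.** A reader might infer that RDT shops are tied to one product while control shops are not, so a first-line rule would lower the control result by s × 0.50 × p (14 points at s = 40%, p = 70%). The documents do not support this. The product training under Diagnosis and treatment procedures is for private providers in general; only the RDT training in the next paragraph is confined to intervention areas. Ethical issues likewise gives the product training to shopkeepers without distinction. The arithmetic also omits the slide-negatives: the net control change at those values is 0.40 × 0.50 × (1 − 1.40) = −8 points, it is 0 at p = 50%, and it is positive below that.

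**Conclusion.** The point stands as an inconsistency in the definition of the primary composite. For slide-negatives the two versions conflict on any reading of first-line. For slide-positives they conflict only if first-line is narrower than ACT, which the protocol neither says nor excludes.

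No size or direction of bias can be derived. The swings at s = 20% show only that the choice of rule could matter against a planned difference of 26.5 to 28.5 points. They rest on assumed s and p, and they leave out u. An imbalance by arm is possible but not shown. The planned 10 clusters per arm correspond to the ACT-purchase wording.

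**What to change.** 1. Use one definition of the composite, covering slide-positives and slide-negatives together, in Sample size requirements, Evaluation and footnote 1. The Sample size wording is the natural choice because the planning rates are stated as ACT purchase. The two groups must not be repaired separately: ACT for positives combined with no first-line drug for negatives could make another ACT a success whatever the slide shows.
2. State which drugs count as first-line wherever the term is kept.
3. Report a first-line-only version of the whole composite as a sensitivity analysis.
4. Reconcile the Study design paragraph with its table on which product the intervention covers. The choice of product is the sponsor's.

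The cost is wording in three places, one definition, one reconciliation and one extra analysis. No new data are needed, since exit interviews already record the type and quantity of drugs sold.

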### Studies indicate that less than 40% of adults and less than 25% of children visiting a drug shop will purchase an antimalarial.3,4 Conservatively assuming a baseline level of ACT purchase in 50% of consultations, sample size was calculated to demonstrate an increase in appropriate purchase of an ACT among RDT-positive patients to 75%, and a decrease in inappropriate treatment among RDT-negative patients to 20%. A cluster-randomised trial with 90% power at the 95% significance level and variation between clusters k=0.25, will require a total of 10 clusters per arm, with 61 consultations per cluster (a total of 610 consultations in each arm). A minimum of 620 patients within each age group will thus be recruited at participating outlets in each arm, yielding an overall total of 1240 patients aged 0-4y; 1240 aged 5-14y; and 1240 adults (a total of approximately 375 patients per outlet). Sample size calculations, repeated for lower levels of antimalarial purchase at baseline, required <10 clusters per arm.

The unit of randomization is the community, defined as the census enumeration area. The study will thus be conducted in 20 enumeration areas in two neighbouring sub-counties within Mukono District. Registered drug outlets located in the 10 enumeration areas randomized to the intervention will be trained in the use of RDTs, and drug outlets located in the other 10 enumeration areas will continue their current practice (presumptive diagnosis and treatment).

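### The 50% baseline is conservative, and fewer than 10 clusters suffice at lower baselines, only for the rise in test-positives; both assurances fail for over-prescription at the protocol's own 25% figure for children

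*Protocol*

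**What the plan says.** All of this is in the Protocol, section (c), mostly under Sample size requirements.

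- **Endpoint sized.** "Sample size requirements for a cluster-randomised trial15 were calculated for the primary endpoint of the proportion of patients receiving appropriate treatment". The next sentence makes it a composite: "Appropriate treatment is defined as a composite including both a) those who are slide-positive who purchase an ACT", together with slide-negative patients who buy no antimalarial.
- **Evidence on baseline.** Studies are cited that "less than 40% of adults and less than 25% of children visiting a drug shop will purchase an antimalarial".
- **Assumption and targets.** The calculation proceeds by "Conservatively assuming a baseline level of ACT purchase in 50% of consultations". It aims at "an increase in appropriate purchase of an ACT among RDT-positive patients to 75" per cent, and at a fall in inappropriate treatment of RDT-negative patients to 20%.
- **Result.** With 90% power and k = 0.25, the trial "will require a total of 10 clusters per arm, with 61 consultations per cluster". The resulting 610 per arm (rounded up to 620) is then applied to each of three age groups.
- **Assurance.** "Sample size calculations, repeated for lower levels of antimalarial purchase at baseline, required <10 clusters per arm".

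Under Primary endpoints, over-prescription in patients who are not parasite-positive is listed as a primary endpoint in its own right. All endpoints are to be reported by age group, and the stated purpose of the between-arm comparison is to learn whether testing reduces overuse in each group.

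**The concern.** The two targets move in opposite directions. Purchase has to rise among positives and fall among negatives. A lower baseline widens the first gap (to 75%) and narrows the second (to 20%). One baseline therefore cannot be conservative for both, and repeating the calculation at lower values cannot reduce the cluster requirement for both.

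The cited baselines lie below the 50% assumed, and the lowest is for children. They are also upper limits, and they refer to any antimalarial, so ACT purchase alone cannot be higher. A reader of the assurance would conclude that the more likely, lower baselines are safe. If that is untrue for over-prescription, a null result in children would be read as no effect when the trial had little chance of showing one.

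**Working it through.** **Inputs from the protocol.** k = 0.25; m = 61 per cluster; 10 clusters per arm; 90% power; targets of 75% (positives) and 20% (negatives); baselines of 50% (assumed), 40% (upper limit, adults) and 25% (upper limit, children).

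**Assumptions.** The test is two-sided at 5%. The targets stay fixed at 75% and 20% when the baseline changes. The protocol prints no formula, so I use the usual coefficient-of-variation formula for unmatched clusters:

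c = a + 10.507 × V / (p0 − p1)², where V = p0(1 − p0)/m + p1(1 − p1)/m + k²(p0² + p1²)

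Here 10.507 = (1.96 + 1.2816)², and a is 0 or 1 (without or with the small-number term). Power with 10 clusters is Φ(√[(10 − a)(p0 − p1)²/V] − 1.96). Ranges below run across the two values of a.

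**Step 1: the plan's own figure, 50% to 75%.** V = 0.4375/61 + 0.0625 × 0.8125 = 0.05795. Then 10.507 × 0.05795/0.0625 = 9.74, which is 10 clusters (90.7% power) without the extra term. With it the result is 10.74 (87.6%). The stated 10 reproduces.

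**Step 2: lower baselines, component by component (m = 61).**

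| Baseline | Positives to 75%: c | Negatives to 20%: c | Negatives: power with 10 |
|---|---|---|---|
| 50% | 9.74 / 10.74 | 2.90 / 3.90 | above 99% |
| 40% | 4.47 / 5.47 | 5.01 / 6.01 | 99% or more |
| 30% | 2.45 / 3.45 | 14.91 / 15.91 | 76% / 71% |
| 25% | 1.90 / 2.90 | 50.87 / 51.87 | 30% / 28% |

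(Without / with the extra term; round c up.) Worked case, 25% to 20%: V = 0.3475/61 + 0.0625 × 0.1025 = 0.01210, and 10.507 × 0.01210/0.0025 = 50.87. The negative component passes 9 clusters once the baseline falls to about 34–35%. At 20% or below, the target is no reduction at all.

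**Step 3: does cluster size rescue it?** No. With unlimited patients per cluster, 25% to 20% still needs 10.507 × 0.0625 × 0.1025/0.0025 = 26.9, so 27–28 clusters. Whether 61 counts all consultations or only one test-result group does not change the conclusion.

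**Step 4: the composite.** Write b for baseline purchase and q for the share of patients who are positive. Then p0 = qb + (1 − q)(1 − b) and p1 = 0.75q + 0.80(1 − q), taking test and slide as agreeing and applying k to the proportion treated appropriately. The protocol gives no q, so the values below are assumptions.

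| b | q | p0 to p1 | Clusters | Power with 10 |
|---|---|---|---|---|
| 50% | 50% | 0.500 to 0.775 | 9–10 | 92–94% |
| 40% | 30% | 0.540 to 0.785 | 12–13 | 83–87% |
| 40% | 50% | 0.500 to 0.775 | 9–10 | 92–94% |
| 25% | 30% | 0.600 to 0.785 | 21–22 | 57–61% |
| 25% | 40% | 0.550 to 0.780 | 13–14 | 78–82% |
| 25% | 50% | 0.500 to 0.775 | 9–10 | 92–94% |
| 25% | 60% | 0.450 to 0.770 | 6–7 | 98–99% |

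For 9 clusters or fewer, q must be at least about 45–53% at a 40% baseline and 48–51% at a 25% baseline.

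**The case against.** **The assurance is right for what matters most.** The protocol gives priority to raising ACT purchase among true cases. For that component 50% is the hardest of the cited baselines, and lower ones need 6 clusters or fewer. This stands, and is why the statements should be limited rather than called wrong throughout.

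**Adults are covered.** At a 40% baseline both components need fewer than 10 clusters (5–6 and 6–7). This also stands for the 40% figure itself, although that is an upper limit and the negative component fails from about 34–35% down.

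**The 20% target may have moved with the baseline.** If the same relative reduction (×0.4) had been kept, negatives would need 4–5 clusters at 40% and 5–6 at 25%, and the assurance would hold. The protocol says nothing of the kind. It gives 20% as a level.

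**The composite may be safe.** The site is described as an area of high transmission, and at half or more positive the composite keeps at least 92% power at both cited baselines. That is fair, but positivity is not stated. The result also depends on what k describes: at a 25% baseline and 30% positive, applying k to the proportion treated inappropriately lowers 21.8 clusters to 7.0 (both with the extra term). The composite result is therefore conditional. The over-prescription result is not rescued this way: applying k to the untreated proportion there (75% to 80%) raises the need to about 340 clusters.

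**Stronger readings a reader might infer.** One is that 10 clusters of 61 fail to give 90% power for 50% to 75%. The documents do not support this: the figure is 90.7% or 87.6% depending on a small-number term the protocol does not mention. Another is that 90% holds only at exactly a 50% baseline; the 50% and 60% positivity rows of the composite table show otherwise. A third is that RDT error costs a definite amount of power. The documents give no sensitivity or specificity, so no size can be put on it.

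**Conclusion.** Wrong as written, in a limited way. The two assurances hold for the rise to 75% in test-positives. They fail for the fall to 20% in test-negatives, which is a primary endpoint compared within each age group. At the protocol's own upper limit for children the requirement is about five times the planned clusters, and 10 clusters give less than one chance in three of detecting the target reduction. At lower baselines the position worsens until, at 20%, nothing is left to detect.

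This rests on the fixed 20% target, k = 0.25 applied to the proportion treated, and a two-sided 5% test. It does not depend on the small-number term or on cluster size. The composite finding rests further on an assumed positivity and on the meaning of k, so it shows only that the assurance is unqualified, not that the composite is underpowered.

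A related defect is in the definition. The targets are set by RDT result, but control shops are given no RDTs and the endpoint is scored on the research slide. As worded, the contrast has no counterpart in the control arm.

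**What to change.** Rewrite the sample size paragraph and keep 10 clusters per arm.

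1. Limit the word conservatively and the sentence on fewer than 10 clusters to the test-positive component, or delete both.
2. Define the 75% and 20% targets on slide status, which both arms have.
3. Restate power by age group, for the composite and separately for over-prescription, over baseline purchase of 25–50% and slide positivity of 20–70%. State which proportion k describes and whether the 20% target is fixed or relative.
4. Say that over-prescription in children will be estimated with low power if baseline purchase is near 25%, so that a null result is read from its confidence interval and not as evidence of no effect.

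The 90% figure for 50% to 75% can stand if the formula behind it is stated. The cost is one rewritten paragraph and a less favourable stated power, with no extra clusters or patients.

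### The stated recruitment of about 375 patients per outlet is roughly twice what the protocol's own totals allow (186 per enumeration area), and the recruitment age bands differ from the analysis bands

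*Protocol*

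**What the plan says.** The protocol, section (c), under Sample size requirements, sizes the trial at "A cluster-randomised trial with 90% power at the 95% significance level and variation between clusters k=0.25". It concludes that the trial "will require a total of 10 clusters per arm, with 61 consultations per cluster (a total of 610 consultations in each arm"). It then sets a minimum of 620 patients per age group per arm, which it doubles to 1240 per age group over both arms. The list ends with "1240 aged 5-14y; and 1240 adults (a total of approximately 375 patients per outlet").

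The next paragraph makes the census enumeration area the unit of randomisation, with 10 areas per arm: "The study will thus be conducted in 20 enumeration areas in two neighbouring sub-counties within Mukono District". The number of participating outlets, in total or per area, is not given.

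On age, the quotas in the sample size section are for 0-4, 5-14 and adults, with no lower limit for adults. The text under Primary endpoints in the same section (c) uses other bands: "All endpoints will be examined and reported according to age and sex: children aged 0-4y, 5-15y and adults" of 16 or over. It adds that the arms will be compared within each age group.

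**The concern.** The per-outlet number is the only outlet-level recruitment figure in the protocol, and it cannot be reconciled with the totals beside it. If someone used it as a target, either the trial would recruit about twice the planned patients, with twice the exit interviews and slides, or the planned total would be reached from about half the clusters. The second would matter more, because in this design the number of clusters carries most of the precision.

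The age bands raise a smaller question. The 620 per arm is set separately for each age group, so it should refer to the groups in which the arms are compared. A 15-year-old is outside the 5-14 quota, and so by implication counts as an adult for recruitment, but is analysed in the 5-15 group.

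**Working it through.** **Inputs**, all from Sample size requirements: 10 clusters per arm; 61 consultations per cluster; 620 per age group per arm; three age groups; 20 enumeration areas; about 375 per outlet.

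**The plan's totals, reproduced**
- Requirement per arm: 10 x 61 = 610, rounded up in the protocol to 620.
- Both arms, one age group: 2 x 620 = 1240.
- Both arms, three age groups: 3 x 1240 = 3720.

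These agree with each other and with the protocol.

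**Patients per area**
- Whole trial: 3720 / 20 = 186.
- One arm: 3 x 620 / 10 = 186.
- Per age group: 186 / 3 = 62, against 61 required.
- On the unrounded 610: 3 x 2 x 610 / 20 = 183.

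With one outlet per area the average per outlet is 186; with more outlets it is lower. The ratio is 375 / 186 = 2.02.

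**Can 375 be reached some other way?**
- Both-arm total over one arm's clusters: 3720 / 10 = 372, within 1% of 375.
- The same on the 610 basis: 3 x 2 x 610 / 10 = 366.
- Working back: 375 / 3 = 125 per age group, and 125 x 10 = 1250 per arm. That is close to the 1240 planned for both arms together.

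So 375 is reproduced approximately only when a two-arm total is divided by 10.

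**What 375 would imply**
- At 20 outlets: 375 x 20 = 7500 patients, which is 7500 / 3720 = 2.02 times the plan.
- At a total of 3720: 3720 / 375 = 9.9 outlets in the whole trial, too few to put one in each of 20 areas.

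**Is the cluster count affected?** The usual formula for an unmatched cluster trial with proportions is

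c = 1 + (z_α/2 + z_β)² [p0(1−p0)/m + p1(1−p1)/m + k²(p0² + p1²)] / (p0 − p1)².

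Take p0 = 0.50, p1 = 0.75, m = 61, k = 0.25, two-sided 5% (the protocol does not state sidedness) and 90% power, so (1.960 + 1.282)² = 10.51. The bracket is 0.25/61 + 0.1875/61 + 0.0625 x 0.8125 = 0.0041 + 0.0031 + 0.0508 = 0.0580.
- With the added 1: c = 10.74.
- Without it: c = 9.74, i.e. 10.
- For 50% against 20%: c = 3.90.
- For the composite endpoint (75% correct in positives, 80% in negatives), assuming 20% to 70% of patients are RDT-positive: c = 8.68 to 9.86. At 80% positive it is 10.14.

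Ten clusters per arm is therefore reachable under standard variants, and 375 enters none of these calculations. The between-cluster term is 0.0508 of 0.0580, about 88% of the bracket. Raising m from 61 to 186 moves c only from 10.74 to 9.93, so extra patients per cluster are a poor substitute for clusters.

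**Age bands side by side**

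| | Youngest | Middle | Oldest |
|---|---|---|---|
| Recruitment quotas | 0-4 | 5-14 | adults, no lower limit given |
| Analysis groups | 0-4 | 5-15 | 16 or over |

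The bands differ by one year of age. The margin over the requirement is 620 − 610 = 10 patients per arm per age group, or one per cluster. The protocol gives no age distribution, so the number of 15-year-olds cannot be estimated.

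**The case against.** The best defence is that 375 is a remark in parentheses. The operative figures are 620 per age group per arm, 10 clusters per arm, 61 per cluster and 20 areas. They are coherent, and anyone following them recruits correctly. That stands, and it limits the consequence.

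An outlet is also not a cluster, and the number of outlets is not stated, so no correct per-outlet figure can be derived. That stands too: 186 is a figure per area. It does not rescue 375, because more outlets per area only lower the average per outlet.

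One might add that 620 is a minimum, so over-recruitment is allowed. But the protocol goes on to fix an overall total of 1240 per age group, and 7500 patients contradicts it.

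A reader might infer more than the documents support:
- That the trial is underpowered or its cluster count wrong. The stated 10 and 61 do not use the 375.
- That field teams will work to 375 and leave clusters empty. The protocol ties no site quota or stopping rule to it and says that all 20 areas take part.
- That the origin of 375 is known. Division by 10 is the likely explanation, but 372 is not 375 and the protocol does not show the step.
- That the age mismatch leaves the group aged 16 or over short. It could, but placing 15-year-olds among adults is itself an implication, and the effect is probably small.

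**Conclusion.** The per-outlet figure is wrong as written. The protocol's own totals give 186 patients per enumeration area, and 375 is 2.02 times the largest possible average per outlet. This rests on one assumption, that each of the 20 areas has at least one participating outlet, which 10 contributing clusters per arm require. The harm is conditional on the figure being used: about 7500 patients at 20 outlets, or 3720 from about 10 outlets. It is a cheaply corrected error in a stated recruitment size and does not undermine the design.

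The age bands are a genuine but minor inconsistency, one year of age wide, whose effect cannot be quantified from the protocol.

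**What to change.** Under Sample size requirements, replace the per-outlet figure with: approximately 186 patients per enumeration area (62 in each age group), shared across its participating outlets. If a per-outlet target is wanted, state the number of participating outlets in each area and derive it from that.

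Use one set of age bands under Primary endpoints and Sample size requirements, for example the analysis bands 0-4, 5-15 and 16 or over, so that 620 per group per arm applies to the groups that are compared.

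Both are wording changes and leave the planned total of 3720 as it is. The protocol does not say whether staffing, test supplies or slide reading were planned on 375 per outlet, so that should be checked when the figure is corrected.
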